## Abstract

**Background:**

Coronary artery bypass graft surgery (CABG) is an effective and widespread coronary revascularisation technique, nevertheless there are a number of long-term postoperative complications from which patients can suffer. One year after CABG surgery pulmonary function is decreased by 12% and 30% of the patients suffer from chronic thoracic pain. To date and to our knowledge there are no effective treatments for these conditions. The aim of the present clinical trial is to explore the effectiveness of osteopathic treatment on these conditions.

**Methods:**

The study is designed as a randomised controlled trial with two parallel groups. Group A will receive a standard cardiac rehabilitation programme during 12 weeks and group B will receive the same standard cardiac rehabilitation programme supplemented with four osteopathic treatments (OT). OT will be performed at week 4, 5, 8 and 12 after surgery. Three hundred and eight patients (Group A: *n* = 154, Group B: *n* = 154) will be enrolled from the cardiothoracic surgery department of the Jessa Hospital Hasselt. Blinding will be assured for the staff of the cardiac rehabilitation centre and outcome assessors. Primary outcome measure will be the mean difference in change from baseline in slow vital capacity (SVC) at 12 weeks after surgery between groups. Secondary outcome measures will be the change from baseline in quality of life, pain, thoracic stiffness and maximal aerobic capacity at 12 weeks after surgery. A follow-up is planned 52 weeks after surgery for SVC, quality of life, pain and thoracic stiffness. Intention to treat analysis will be executed.

**Discussion:**

The OstinCare study has been designed to explore the potential long-term added value of osteopathic treatment in the management of decreased pulmonary function, chronic thoracic pain and diminished thoracic mobility after CABG surgery.

**Trial registration:**

The protocol has been retrospectively registered on ClinicalTrials.gov (NCT01714791).

## Background

Approximately 640,000 coronary artery bypass graft (CABG) surgery procedures are performed in Europe and the United States each year to restore or optimize myocardial perfusion in coronary artery disease [1, 2]. Worldwide there are approximately over two million open-heart surgeries per year [3]. In this surgical intervention, venous and/or arterial grafts are used to bypass the coronary occlusion or stenosis. Because cardioplegia (induction of temporary cardiac arrest) is routinely used, the patient’s circulation is coupled to a cardiopulmonary bypass and access to the heart is most often achieved by median sternotomy. After CABG surgery, a hospital stay of 1 to 2 weeks is generally required [4, 5].

Although CABG surgery is an effective coronary revascularisation technique, there are a number of postoperative complications from which patients can suffer. For example, a decrease in pulmonary function is a frequently observed complication after CABG surgery. During the first week after CABG surgery vital capacity (VC) decreases by 30–60% [6–9] and even up to 1 year this remains reduced by 12% [10, 11]. Reduced VC has a negative effect on exercise tolerance (Vo2max) [12] and therefore it is important to optimize pulmonary function after CABG surgery. No method of postoperative therapy has been distinguished in treating or preventing these long-term changes [6].

In addition, Ragnarsdòttir et al. [8] found a diminished mobility of the left hemithorax at 3 months after CABG surgery. This decreased thoracic mobility was still present 12 months after surgery [11]. Thoracic mobility and vital capacity were affected more when the left internal thoracic artery (LITA)-retractor was used and reduced thoracic mobility is related to a diminished pulmonary function [10].

Chronic pain, which is defined as pain without apparent biological value that has persisted beyond the normal tissue healing time, which usually takes 3 months [13] after CABG surgery. Chronic pain after CABG surgery is described in several studies reaching a time period from 3 to 28 months [14–20]. Kehlet et al. [14] reported a pain prevalence of 30–50%, from which 5–10% suffer from severe disabling pain after more than 6 months after surgery. Numerous other studies report a pain prevalence of 28–56% from 3 to 28 months after CABG surgery [15–20]. Many theories for its cause have been proposed in literature, but the aetiology is still not clear and no therapy or technique has been shown to reduce chronic pain after CABG surgery [17, 21]. In literature this syndrome is described as chronic chest pain [19], chronic thoracic pain [18], chronic post-sternotomy pain [14–20].

Chronic pain after CABG surgery is a major clinical problem, which is distressing and reduces the quality of life of patients [14].

As a result, many patients undergoing CABG surgery suffer from decreased pulmonary function, reduced thoracic mobility and/or chronic thoracic pain. These anomalies have significant clinical repercussion and may have an effect on the patients’ quality of life [14].

According to current clinical guidelines, exercise intervention should be initiated early after CABG surgery [22]. According to these recommendations, exercise training should be individually tailored according to the clinical condition, baseline exercise capacity and ventricular function. Upper-body training can begin when the sternal wound is stable. The general applicable exercise training in cardiac rehabilitation consists of walking, jogging, cycling, swimming, rowing, stair climbing, elliptical trainers and aerobic dancing, at low to moderate exercise intensity, for 3–5 days/week. Programmes should last up to 12 weeks for outpatient settings. However in this trajectory, pulmonary function, thoracic pain and thoracic mobility are not specifically targeted.

In fact, to our knowledge there are no effective treatments to treat the latter conditions or effective preventive interventions. Osteopathic treatment (OT) has been used to treat and manage pain symptoms. Several articles have been published addressing acute and chronic pain in different medical conditions [23–25]. However, no trials have been conducted to test the effect of OT on chronic pain after CABG surgery.

## Methods/Design

### Aim of the study

The aim of this randomised controlled trial is to examine whether OT could lead to a better treatment of chronic thoracic pain, decreased pulmonary function and/or decreased thoracic mobility.

We hypothesized that OT reduces the decrease in SVC, reduces chronic thoracic pain, reduces thoracic stiffness and improves the quality of life in patients at 12 weeks and 52 weeks after CABG surgery.

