#### Osteopathic procedure

The protocol used for OT and osteopathic examination (OE) incorporates a number of osteopathic techniques and will be performed by five registered osteopaths with a minimum experience of 5 years. The protocol used is based on the work of Dickey [31] and supplemented with the findings of other authors [32–35]. The most common findings found in literature are:Decrease in costal mobility [8, 10, 11, 36]Decrease in pulmonary function [6, 8, 10]Decreased thoracic mobility [8, 10, 11, 31]Dysfunction of the abdominal diaphragm [31, 37–41]

The nomenclature, indications and contraindications for the OE and OT are based on the work of Nicholas and Nicholas [32], Chila [42], on the professional competence profile of an osteopath [43–45] and the benchmarks of the World Health Organisation [46].

The OE protocol is a set of standardised test for a first evaluation of the patient. The findings are noted on a predefined Microsoft excel-file by the Osteopath.Inspection: in standing, seated and supine: observe the patient in posterior, anterior and lateral view to develop the most complete understanding of the patients makeup before performing the remainder of the OE ([32] p. 3–14).Position test of the thoracic spine (seated) ([42] p.561)Intersegmental motion testing:thoracic seated ([32] p. 42–49)cervical supine ([32] p. 60–65)costal supine ([32] p. 52–59
Costal motion testing supine [32] (p.53–56)Evaluation of the abdominal diaphragm (seated and supine) ([42] p. 567)

The OT consists of a standardised treatment protocol (Table 1) and a supplementary treatment protocol of the dysfunctions found during the examination. In order to be reproducible, the different treatment possibilities are discussed and presented (Fig. 3). The OT will take 30–45 min. The examination room is air-conditioned and has a constant temperature of 21–22 °C. The OT will be performed at 4 weeks postoperative (t_1_), 5 weeks postoperative (t_2_), 9 weeks postoperative (t_3_) and at 12 weeks postoperative (t_4_). OT can be considered as safe, and major adverse events are very rare [47, 48]. In case adverse events should occur, they will be recorded and discussed in the final paper.

**Table 1 Tab1:** Standard treatment protocol OstinCaRe study

Osteopathic technique	Description	Rationale for use

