#### MacNew quality of life questionnaire (QLQ) and Visual analogue scale (VAS)

The Flemish version of the MacNew QLQ and the VAS for pain and thoracic stiffness are delivered to the patients by a blinded person of the cardiac rehabilitation centre at enrolment (t_0_), 12 weeks after surgery (t_4_) and at 12 months after surgery (t_5_). The Flemish version of the MacNew QLQ demonstrates good psychometric properties and is recommended as a specific instrument for assessing and evaluate health-related quality of life in Flemish-speaking patients [52].

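### All four treatments and the week-12 pain score fall before, or at best at, the protocol's own 3-month threshold for chronic pain, so they cannot show treatment or week-12 reduction of chronic pain

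*Protocol article*

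**What the plan says.** All references are to the protocol article.

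- **Definition.** The Background describes chronic pain as "pain without apparent biological value that has persisted beyond the normal tissue healing time, which usually takes 3 months". It cites prevalences of 28–56% in studies running from 3 to 28 months after CABG.
- **Aim.** Under Aim of the study, the trial examines "whether OT could lead to a better treatment of chronic thoracic pain", along with pulmonary function and thoracic mobility.
- **Hypothesis.** The same section expects that OT "reduces chronic thoracic pain, reduces thoracic stiffness and improves the quality of life in patients at 12 weeks and 52 weeks after CABG surgery".
- **Treatment times.** The Abstract says "OT will be performed at week 4, 5, 8 and 12 after surgery". The Osteopathic procedure section gives weeks 4, 5, 9 and 12. The third session thus differs between the two places. They need to be reconciled, but the difference does not affect this point.
- **Pain measurement.** The outcome is change in VAS pain from baseline at 12 and 52 weeks (Outcome measures). The VAS is given at t0, week 12 and 12 months (section on the MacNew questionnaire and VAS), and the legend to Fig. 2 places t0 at 3 weeks after surgery.
- **Population.** Participants admits patients for elective CABG by median sternotomy. No inclusion or exclusion criterion concerns pain.

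**The concern.** The aim, the definition and the schedule do not fit together. To treat chronic pain, patients must have it when they are treated, and to reduce chronic pain at week 12, pain must be able to count as chronic by then. Under the protocol's own definition neither holds. The week-12 change score starts from pain three weeks after a sternotomy and ends about when healing is expected to be complete. It describes how fast postoperative pain settles.

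What is at stake is the conclusion. With the hypothesis worded as it is, a between-group difference in week-12 VAS would confirm a hypothesis about chronic pain, although the data concern healing-phase pain. The Background says no therapy has been shown to reduce chronic pain after CABG, so such a claim would carry weight. The question the design can answer, whether early treatment of all comers leads to less late pain, is not the one the Aim states.

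**Working it through.** **1. Timing against the definition.** Weeks are converted to days after surgery (weeks × 7). Three calendar months are 89 to 92 days, on average 365.25 / 4 = 91.3 days, or 13.0 weeks.

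| Event | Week | Day | Against day 89–92 |
|---|---|---|---|
| VAS baseline (t0) | 3 | 21 | before |
| OT 1 | 4 | 28 | before |
| OT 2 | 5 | 35 | before |
| OT 3 | 8 or 9 | 56 or 63 | before |
| OT 4 | 12 | 84 | 5–8 days before |
| VAS follow-up 1 | 12 | 84 | 5–8 days before |
| VAS follow-up 2 | 52 | 364 | 272–275 days after |

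Four of four treatments and one of two follow-up VAS scores precede the threshold. The article also uses 12 weeks and 3 months for the length of the same rehabilitation programme. If the two are taken as equal, OT 4 and the week-12 VAS fall at the threshold, OT 1 to 3 still fall before it, and the definition asks for pain beyond it. The baseline stays at day 21 on either reading.

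**2. Population.** At a prevalence of 28–56%, 44–72% of unselected patients would not have chronic pain at a given late assessment. Any effect confined to those with pain is diluted in the overall mean.

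**3. What dilution could mean (assumed values, illustration only).** The protocol gives no VAS figures. Assume that at 52 weeks patients with pain have mean 40 and SD 20 on a 0–100 scale, all others score 0, and OT lowers pain by 12 points in those with pain. Evaluable n per group is 154 × 0.8 = 123. For prevalence p, the effect is 12p and the variance is p(20² + 40²) − (40p)².

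- p = 0.28: effect 3.4 points; variance 560 − 125.4 = 434.6, SD 20.8; d = 0.16; power 24%.
- p = 0.56: effect 6.7 points; variance 1120 − 501.8 = 618.2, SD 24.9; d = 0.27; power 56%.

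(Two-sided t-test, alpha 0.05. The SD is that of the VAS level, not of the change from t0.)

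**4. Would a proportion with pain do better?** Same scenario, with normal scores among those with pain, comparing the proportion above a cut-off by the arcsine effect size with 123 per group:

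| Cut-off | Power, p = 0.28 | Power, p = 0.56 |
|---|---|---|
| 10 | 9% | 18% |
| 20 | 17% | 38% |
| 30 | 28% | 59% |
| 40 | 36% | 68% |
| Mean VAS, for comparison | 24% | 56% |

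Low cut-offs lose power against the mean and higher ones gain some. Steps 3 and 4 bear only on how to analyse week 52. The timing result in step 1 does not depend on them.

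**The case against.** The best case for the plan has four parts.

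- **The outcome list is neutral.** Outcome measures speaks of change in pain, not chronic pain, and the Discussion expects a reduction in thoracic pain. That is correct, and it makes the repair easy. But the hypothesis names chronic pain at 12 weeks, and the hypothesis is what the results will be read against.
- **Week 12 is a near miss.** It is about one week short of 3 months, the article treats the two as equal, and the definition says usually. This stands as far as it goes: week 12 should not be called clearly inside the healing window. It still does not lie beyond the threshold, and the change is measured from week 3.
- **Week 52 is well past the threshold.** This stands in full. A reader might infer from the timing that the trial can say nothing about chronic pain. The documents do not support that: the 52-week VAS is a listed outcome, is named in the hypothesis and is taken in all randomised patients. Treating everyone early and comparing pain at one year is a sound test of prevention or reduction of later pain.
- **Dilution is not established.** A reader might also infer that most patients will never have chronic pain, so the mean VAS must give way to a proportion. At 56% prevalence those with pain are the majority, prevalence at varying times does not say who never has pain, and the power figures rest on assumed scores. Under those same assumptions the proportion can do worse than the mean.

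**Conclusion.** The point holds for the aim and for the week-12 claim. By the protocol's own definition, no participant has chronic post-CABG pain at baseline or during the first three treatments, and the fourth treatment and the week-12 VAS come 5–8 days before the threshold or at best at it. The trial cannot show treatment of established chronic pain, and the week-12 VAS is a measure of postoperative (subacute) pain.

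It does not hold for week 52, which remains a valid randomised comparison of late pain. The lack of a pain criterion is no fault for a prevention question; it only rules out reading the result as treatment of existing chronic pain. The sensitivity of the 52-week mean is uncertain, because the 24–56% power depends on VAS values the protocol does not give.

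The scope is one secondary outcome and the wording of the aim and hypothesis. The primary SVC endpoint is untouched.

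**What to change.** 1. In Aim of the study, restate the pain part of the aim and hypothesis as prevention or reduction of later chronic thoracic pain, assessed at 52 weeks.
2. Describe the week-12 VAS as postoperative pain and base no chronic-pain claim on it.
3. Rest the chronic-pain conclusion on the 52-week VAS, compared between all randomised patients by group with adjustment for the t0 VAS. With that adjustment, analysing the 52-week level or the change from t0 gives the same group difference, so the listed outcome can stay.
4. Optionally, add the proportion with 52-week pain above a cut-off fixed before unblinding, as a supportive analysis. It should not replace the continuous outcome, since it gains or loses power depending on the cut-off.

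The cost is small: a change of wording and one adjusted analysis of data already planned, with no new visit, patient or measurement. The protocol already provides for notifying modifications to the registry and the journal. The price is that a week-12 difference in pain can no longer be presented as a result on chronic pain.

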### Design

OstinCaRe stands for Osteopathy in Cardiac Rehabilitation. The OstinCare-study is designed as a randomised controlled trial with two parallel groups. Group A will receive a standard exercise-based cardiac rehabilitation programme and group B will receive a standard exercise-based cardiac rehabilitation programme with four additional osteopathic treatments. The study will be performed at the Jessa Hospital Hasselt, Belgium.

### Participants

Subjects admitted to the hospital for elective CABG with median sternotomy will be eligible for this study. Participant recruitment began in January 2010 and is expected to finish in December 2017. Subjects with diagnosed chronic obstructive pulmonary disease, diagnosed neurologic disease that prevents participation in the cardiac rehabilitation programme, diagnosed nephrological disease that requires haemodialysis, prior thoracic surgery, surgery in the epigastric, right or left hypochondriac region will be excluded. Subjects will also be excluded if the subject has a prolonged stay (>5 days) in the intensive care unit. All CABG surgery procedures will be performed by the same surgical team. Subjects may not receive any other manual treatment on the spine and/or thorax during the study.

### Randomisation and masking

Patients will be randomly assigned in a 1:1 ratio to either group A or group B (Fig. 1). A blocked allocation schedule will be used. Randomisation will be performed by means of opaque, sealed envelopes. A physical therapist of the cardiac rehabilitation centre will perform and store the randomisation. The personnel of the cardiac rehabilitation centre performing the outcome measurements in this study are unaware of patient’s allocation. Osteopathic treatments will not be performed in the presence of the personnel of the cardiac rehabilitation centre. The treatments will be performed in another location to assure that the personnel of the cardiac rehabilitation centre remains blinded to patient’s allocation. Only the treating osteopaths will be aware of the patient’s allocation. The enrolment and procedures are visualised in Fig. 2 according to the Standard Protocol Items: Recommendations for Interventional Trials (SPIRIT) guidelines [26, 27].

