## Discussion

Although CABG surgery is an effective coronary revascularisation technique, there are a number of postoperative complications, such as diminished pulmonary function and chronic thoracic pain, from which patients are prone to suffer from [10, 11, 14–20]. To our knowledge, there are no effective treatments to treat these conditions or effective preventive interventions [6, 17, 21]. The OstinCaRe study has been designed to explore the potential long-term added value of OT in the management of decreased pulmonary function, chronic thoracic pain and diminished thoracic mobility after CABG surgery. The present study is the first study to examine long-term effects of OT after CABG surgery using rigorous procedures and gold standard methods for clinical trials. Previous studies studied the short-term effects of OT after CABG surgery. One study has proven that OT has immediate, beneficial haemodynamic effects after CABG surgery when administered while the patient is sedated [34]. Another study mentioned beneficial, though statistically insignificant, effect of OT on length of stay and recovery of bowel function of CABG surgical patients [54].

The expected outcomes from the present study will be increased pulmonary function, reduction in thoracic pain and increased thoracic mobility. The study has the potential to deliver the first valuable complement in cardiac rehabilitation programmes to address these problems.

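### The statement that only the osteopaths know the allocation is false as written: patients and the therapist who performs the randomisation know it too, so pain, stiffness and MacNew are unblinded self-reports.

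*Protocol article*

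**What the plan says.** The section Randomisation and masking says "Only the treating osteopaths will be aware of the" patient's allocation. The same section says "A physical therapist of the cardiac rehabilitation centre will perform and store the randomisation". It also says that the centre's personnel who take the outcome measurements do not know the allocation, and that osteopathic treatment (OT) is given elsewhere and out of their presence.

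The abstract's Methods paragraph says "Blinding will be assured for the staff of the cardiac rehabilitation centre and outcome assessors". Under Statistical analysis, the statistician is also described as blinded.

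The arms are set out under Design: "Group A will receive a standard exercise-based cardiac rehabilitation programme", whereas "group B will receive a standard exercise-based cardiac rehabilitation programme with four additional osteopathic treatments". Under Osteopathic procedure, "The OT will take 30–45 min", and Table 1 shows that every standard technique is hands-on. The text describes no sham, placebo touch or matched individual contact for group A.

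Pain VAS, stiffness VAS and MacNew are secondary outcomes at 12 and 52 weeks. The section on these instruments says that they "are delivered to the patients by a blinded person of the cardiac rehabilitation centre".

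**The concern.** A patient either is or is not treated by an osteopath on four occasions, so each patient knows the arm. The sentence on who knows the allocation therefore cannot be true. The therapist who performs the randomisation is a second exception to it.

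This matters most where the patient does the rating. Pain, stiffness and quality of life are part of the hypothesis under Aim of the study, so they are not peripheral. Expectation and extra individual contact can shift such ratings without any specific effect of the techniques. A reader who relies on the stated masking could take a difference in these outcomes for a blinded comparison.

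There is a lesser consequence for the staff-measured outcomes. Patients who know their arm train with the centre's staff 3 days a week for 3 months. Keeping the treatment out of sight does not stop a patient from mentioning it.

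**Working it through.** No stated figure has to be reproduced. The main check sets the statements side by side.

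1. **Who knows the allocation.** Stated: the treating osteopaths only. Implied by Design and Osteopathic procedure: every patient, because OT is an overt add-on with no sham. Stated in the same section: a therapist of the centre performs the randomisation. The word *only* fails on both counts. The abstract's assurance for the centre's staff also fails for this therapist, who is one of them.

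2. **Who assesses each outcome.**
   - SVC and VO2max: measured by staff who are described as unaware of allocation. Staff blinding is possible here, provided that the therapist holding the randomisation takes no measurements. The article does not say so explicitly.
   - Pain VAS, stiffness VAS and MacNew: scored by the patient. The blinded person only delivers the form. The assessor is the patient, who is unblinded.

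3. **Difference in contact between the arms.**
   - Extra in group B: 4 × 30 min = 2 h, to 4 × 45 min = 3 h.
   - Common to both arms (Cardiac rehabilitation programme; 3 months taken as 12 weeks): 3 × 12 = 36 sessions; 36 × 45 min = 1,620 min = 27 h.
   - Ratio: 2/27 = 7% to 3/27 = 11% more contact time in group B, all of it individual and hands-on.

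4. **Illustration of what a reporting bias could do.** The size of the bias is an assumption; the article gives none. Suppose no true effect and a shift of d SD in a self-reported score, with a two-sided 5% test and no multiplicity correction.
   - Number analysed: 154 × (1 − 0.20) = 123 per group.
   - Standard error of d: √(2/123) = 0.1275.
   - d = 0.2: P(Z > 1.96 − 0.2/0.1275) = P(Z > 0.39) = 0.35.
   - d = 0.3: P(Z > 1.96 − 0.3/0.1275) = P(Z > −0.39) = 0.65.
   - With all 154 per group analysed, the same calculation gives 0.42 and 0.75. For a shift of 0.1 SD it gives 0.14.

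**The case against.** The case on the other side is substantial, and much of it stands.

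- **The article never says that patients are blinded.** A reader might infer that it claims this, or that it calls pain, stiffness and MacNew blinded outcomes. It does neither. The abstract names only staff and assessors, and the sentence on the osteopaths closes a run of sentences about personnel. It could be meant as *among those who treat or measure*. Even so, it is false for the therapist who performs the randomisation, and nowhere does the article say that patients are unblinded.
- **Group A is not without attention.** A reader might see the contrast as attention against none. The roughly 27 hours of supervised training, with counselling and psychosocial management, are common to both arms. What is unmatched is 2 to 3 hours of individual contact.
- **An open add-on design is legitimate.** The Discussion asks about the added value of OT. For that question, contact and context are part of what is added. Nothing in the article makes a sham necessary.
- **Real protections exist.** Treatment is given in a separate location and out of the staff's presence, the primary outcome is measured by blinded staff, and the statistician is blinded. A reader might conclude that the primary comparison is unblinded in the same way. The text does not support that, although SVC and VO2max depend partly on patient effort.
- **The illustration is not the planned analysis.** The protocol specifies Bonferroni correction, which would lower the rates. It also specifies intention to treat with last observation carried forward, which could bring the analysed number nearer 154 and raise them.
- **An article may leave procedures to the full protocol.** A non-disclosure instruction may exist there. Its absence here is not an error by itself; it enters only as part of the remedy.
- **The general claim in the Discussion**, "using rigorous procedures and gold standard methods for clinical trials", is rhetoric rather than a statement about masking, and carries no weight either way.

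**Conclusion.** The masking statement is wrong as written and should be corrected. Patients know their arm, and the therapist who performs the randomisation is a further exception. The assurance that outcome assessors are blinded does not hold for pain VAS, stiffness VAS and MacNew. It can hold for SVC and VO2max, if the therapist takes no measurements and patients do not disclose.

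The conclusion rests on the text's description of the arms, which includes no sham; the figures were not available. It requires no numerical assumption. The 35% to 65% depends wholly on an assumed bias of 0.2 to 0.3 SD, without multiplicity correction, and should not be read as the trial's false-positive rate. The direct effect is on the interpretation of secondary outcomes. No planned test or primary endpoint has to change.

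**What to change.** 1. In the abstract and under Randomisation and masking, state that patients, osteopaths and the therapist holding the randomisation are not blinded, that this therapist takes no outcome measurements, and that the staff measuring SVC and VO2max and the statistician are blinded.
2. Label pain VAS, stiffness VAS and MacNew as unblinded self-reports. Limit conclusions on them to the effect of adding OT sessions to rehabilitation, including contact and expectation.
3. Before each measurement, instruct patients not to reveal their arm to rehabilitation staff.
4. Optionally, have the assessor record a guess of the arm at 12 weeks (t4) and report it. Recruitment is described as running from January 2010 to December 2017, so this can cover only the patients still to reach that visit.

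The cost is revised wording, one instruction line and, if adopted, one tick box. No sham arm, extra visit or extra staff is needed. The downside is a more modest claim on the secondary outcomes.
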